### Sample size consideration

The efficacy assessment is based on the following main judgement criterion: developments between inclusion (week 0) and two years (week 96) of the percentage of glycated haemoglobin HbA1c (%).

The expected benefit is a decrease at two years of at least 1% in the average HbA1c between the group “structured on-going SME support” and the control group “Initial structured education cycle only”. An absolute difference of 1% at two years between the two groups appears relevant [23,24,29,32,39,60-62].

To show an absolute difference of 1% of HbA1c, with a standard deviation of 2.5%, a type I error rate of 5% and a power of 80%, it is necessary to include 99 subjects per group in a bilateral situation.

Because of an estimated data deficiency of 20% at two years (drop out, refusals, deaths), it is planned to include 120 subjects per group, making a total of 240.

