### Control arm: group-based initial structured education cycle only

In the control arm, patients receive only the initial structured education programme, conducted in the 12-week period following inclusion.

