### Outcomes

The main outcome is the evolution of HbA1c (%) at two years. The HbA1c will be measured by the HPLC method in a centralised laboratory (biochemistry laboratory of the Félix Guyon hospital in St Denis).

The secondary outcomes will be as follows: quarterly evolution of HbA1c (%), fasting blood glucose, anthropometric indicators (body mass index, waist circumference), blood pressure, tobacco consumption, annual screening of lipids (total cholesterol, triglycerides, HDL and LDL cholesterol), antidiabetic treatments (type and dose) and the occurrence or worsening of diabetic complications. Health practices (level of physical activity and food consumption) will be assessed by means of annual questionnaires. These have been used in Reunion Island for a number of descriptive or intervention studies: RECONSAL [50], REDIA-prev1 [51] and REDIA-prev2 [31]:

Physical activity: physical activity scores will be assessed by means of a questionnaire developed on the basis of the Baecke self-questionnaire [52], which explores professional, sporting and leisure exercise. Questions on domestic activity were added to our studies.

Food consumption: food consumption (reported energy intake, macronutrient intake, dietary habits) will be assessed by means of a rapid food frequency questionnaire relating to weekly consumption [53]. Quantities of various foods are assessed by means of a photo album. The validity of the questionnaire and the photo album for the population of Reunion was checked by comparison with food surveys.

The care and treatment courses will be assessed by means of questionnaires at inclusion and at two years, based on the questionnaire used in the French ENTRED study [54] adapted to the situation and context in Reunion and comprising 30 items.

Quality of life will be assessed annually by means of the Diabetes Quality of Life, Brief Clinical Inventory [55]. This scale, including 15 items and translated into French for Reunion, was validated for this trial among a sample of 150 Reunion’s patients presenting diabetes.

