### Blinding

For all patients, the first phase (group-based initial education cycle) will be conducted blind with regard to the randomisation arm for patients, until 12 weeks at the latest, researchers and education team. At the end of this first phase the follow-up will therefore be unblinded.

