### Statistical methods

The statistical analyses will be carried out at the CIC-EC in Reunion, under SAS® (version 9.2, SAS Institute Inc., Cary, NC, USA).

Description of the initial characteristics of the screened patients and of the included patients will be done by usual statistics (number, percentage, average ± standard deviation or median and range).

Effective implementation of the SME program and the effective participation will be documented.

The assessment of efficacy of the intervention will be performed in a single analysis, according to the intention to treat principles (*i.e.* according to group allocated by randomisation) with type I error equal 5%, and bilateral formulation of Student t-test (primary analysis).

In the two compared groups, the deficient data on HbA1c (%) at two years (week 96) will be replaced by the measurement obtained at week 84.

If the primary analysis shows a significant difference between the two groups, a comparison of the mean change in HbA1c (%) S96-S0 will be done by the level of participation (secondary analysis using 1-factor ANOVA model): i) basic level ("initial structured therapeutic education only"), ii) level 1 (“structured on-going SME support” without specific additional focused sessions), iii) level 2 (“structured on-going SME support” with specific additional focused sessions).

Analysis of longitudinal data gathered during two years will used in generalised estimating equations (GEE) adapted to repeated measurements in order to test the trends described over the duration of the supervision.

Analysis of the time between randomisation and occurrence of a level of HbA1c <7% (first event observed) will be performed by the Kaplan-Meier method, with comparison of survival curves between groups by Log-rank test.

At each annual collection point the anti-diabetic treatments will be classified into four hierarchical categories: 1) non-insulin antidiabetic monotherapy, 2) non-insulin antidiabetic bi-, tri- (or more) therapy, 3) one injection of insulin, 4) two or more injections of insulin. Between two collection points, moves from one category to a higher (or lower) category will be identified as a reinforcement (or reduction) of the treatment. The interaction between the intervention and treatment category will be tested in the appropriate multivariate models (ANCOVA, GEE, time-dependent variable in the Cox model).

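### The unadjusted t-test on week-0 to week-96 HbA1c change is valid, but leaves out HbA1c measured before the arms diverge and so gives up precision

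*Protocol article*

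**What the plan says.** Under Sample size consideration, the protocol article sets the primary criterion as "developments between inclusion (week 0) and two years (week 96) of the percentage of glycated haemoglobin HbA1c". Under Statistical methods, efficacy is assessed once, by intention to treat, with the "bilateral formulation of Student t-test (primary analysis"). No covariate is named for that test.

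The arms share their first 12 weeks. Under the control arm heading: "In the control arm, patients receive only the initial structured education programme, conducted in the 12-week period following inclusion". The intervention arm receives the same initial cycle, and its first on-going session is at week 16 (Structured group SME intervention, item 3). The Blinding section keeps patients, researchers and educators blind during this cycle, with week 12 as the latest point, and then states: "At the end of this first phase the follow-up will therefore be unblinded".

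HbA1c is collected repeatedly. Outcomes lists "quarterly evolution of HbA1c" as a secondary outcome, and Statistical methods names a week-84 value. The repeated values feed the secondary GEE analysis and, as far as one can tell, the time to HbA1c below 7%. They have no covariate role in the primary test.

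**The concern.** The trial asks whether on-going group support after an initial cycle does better than the initial cycle alone. HbA1c at week 0, and at week 12 if sampled before disclosure, is measured before the arms can differ. Both values probably predict week-96 HbA1c, so using them as covariates would remove outcome variation unrelated to the arm.

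A raw change score uses week 0 only by subtracting it with a fixed coefficient of 1. Unless that happens to be the best coefficient, some precision is lost. Week 12 is not used in the primary test at all.

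What is at stake is the width of the confidence interval and the power, not validity. There is little power to spare: 120 per group with 20% loss leaves 120 x 0.8 = 96, slightly below the 99 required.

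**Working it through.** **Inputs from the protocol article (Sample size consideration).** The difference is 1.0 ("An absolute difference of 1% at two years between the two groups appears relevant"). The other inputs are "with a standard deviation of 2.5%, a type I error rate of 5% and a power of 80" (percent), and the result is "it is necessary to include 99 subjects per group in a bilateral situation". The planned size is 120 per group with 20% missing. The article does not say whether 2.5 is the SD of the change or of the week-96 level.

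**Reproducing the plan's figure.** n = 2 x (1.960 + 0.842)^2 x 2.5^2 / 1.0^2 = 98.1, rounded up to 99 per group. This matches.

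**Assumptions not in the document.** SD of change 2.5; equal HbA1c SD at each visit; correlations r1 = 0.4 (weeks 0 and 96), r2 = 0.55 (weeks 12 and 96), r12 = 0.7 (weeks 0 and 12); 96 evaluable per arm, counting nobody recovered through the week-84 replacement.

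**Step 1, SD of the level.** 2.5 / sqrt(2 x (1 - 0.4)) = 2.28.

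**Step 2, week-0 covariate.** Residual SD = 2.28 x sqrt(1 - 0.4^2) = 2.09. Against the change score, the variance ratio is (1 - r1^2) / (2(1 - r1)) = (1 + r1)/2 = 0.70, a 30% reduction.

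**Step 3, both covariates.** R^2 = (r1^2 + r2^2 - 2 r1 r2 r12) / (1 - r12^2) = (0.16 + 0.3025 - 0.308) / 0.51 = 0.303. Residual SD = 2.28 x sqrt(0.697) = 1.91. The further variance reduction beyond week 0 is 1 - 0.697/0.84 = 17%.

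**Step 4, power and precision at 96 per arm** (noncentral t; half-width = 1.96 x SD x sqrt(2/96)):

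| Primary model | SD | Power for 1.0 | 95% CI half-width |
|---|---|---|---|
| t-test on change from week 0 | 2.50 | 78.7% | 0.71 |
| Week-0 covariate | 2.09 | 90.9% | 0.59 |
| Week-0 and week-12 covariates | 1.91 | 95.1% | 0.54 |

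**Sensitivity of the week-0 gain.** With r1 of 0.3, 0.4 or 0.5, the n per arm for 80% power is 64, 69 or 74, instead of 99.

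**Sensitivity of the week-12 gain.** With r1 = 0.4 and r12 = 0.7, the further cut in residual variance is 3% at r2 = 0.40 (R^2 = 0.096/0.51 = 0.188; 1 - 0.812/0.84), 7% at 0.45, 17% at 0.55 and 24% at 0.60. It also depends on r12: at r12 = 0.90 it is about 5% if r2 = 0.45 but 23% if r2 = 0.55.

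**If 2.5 is the SD of the level.** The change SD is 2.5 x sqrt(1.2) = 2.74, and the three powers for 1.0 become 71%, 85% and 91%.

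**Why not re-base to week 12.** Write the change as A + B, with A from week 0 to 12 and B from week 12 to 96. Its variance is Var(A) + Var(B) + 2Cov(A,B). Using B alone has lower variance only if corr(A,B) > -SD(A)/(2 SD(B)); for SD(A) = 1 and SD(B) = 2.5 that is -1/5 = -0.2. Holding the SD of A + B at 2.5, with assumed SD(A) of 0.5, 1.0 and 1.5:

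| corr(A,B) | n per arm, re-based to week 12 | n per arm, adjusted for A |
|---|---|---|
| 0 | 95 / 83 / 63 | 95 / 83 / 63 |
| -0.2 | 103 / 99 / 85 | 99 / 95 / 82 |
| -0.4 | 111 / 117 / 114 | 94 / 98 / 96 |

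Re-basing can need more than 99 per arm. Adjustment does not in any of these cases.

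**The case against.** The strongest reply is that nothing here is wrong. A t-test on change is valid under randomisation, 99 reproduces, and if 2.5 is the SD of the change, then variation in response to the shared cycle is already in the sample size. All of that stands, and it limits the point to efficiency.

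A second reply is that the size is assumed. The article gives no correlations. If week 12 predicts week 96 no better than week 0 does, the extra gain from week 12 is only about 3% in the case shown. This also stands. The week-0 gain is less fragile: the factor (1 + r1)/2 is below 1 for any correlation short of 1.

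A third reply concerns the week-12 value. The article never names it; it is inferred from quarterly measurement and from week 84 being 7 x 12. Because week 12 is only the latest point for unblinding, some patients could learn their arm before the sample. The timing of randomisation is also unclear: the abstract places it after the initial cycle, while Interventions and Blinding read as an earlier allocation that stays concealed. The week-12 covariate is therefore conditional on the sample preceding disclosure.

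A reader might go further and infer that week 0 is the wrong baseline, or that response to the shared cycle is pure noise in the primary test. The article does not support this. Its Background reports that the benefit of initial education tends to fade after a year. Early response and later change may therefore be negatively correlated, and including the early response can then lower the variance of the change.

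**Conclusion.** The point holds as one of precision. The planned primary test is unbiased and correctly sized for its stated inputs, but it omits covariates that should sharpen it at almost no cost. Under the stated assumptions, power for the design difference rises from about 79% to 91% with week-0 HbA1c, and to 95% with week 12 as well. Most of the gain is therefore ordinary baseline adjustment. The further cut in residual variance from week 12 is about 3% to 24% for week-12/96 correlations of 0.40 to 0.60, and it is available only where the sample precedes disclosure. In large samples, adding the covariate cannot raise the variance.

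These are illustrations, not estimates for this trial, since every correlation is assumed. The documents do not support a claim of bias, of an invalid test, or of a need to move the baseline to week 12.

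**What to change.** - Keep week-96 HbA1c as the outcome and the arm difference as the estimate. Replace the t-test with ANCOVA adjusting for week-0 HbA1c, or with a longitudinal model that has a common baseline mean.
- State when randomisation takes place, whether a week-12 HbA1c is taken, and that it is drawn before the allocation is disclosed.
- Where that order holds, add week-12 HbA1c as a second covariate. Alternatively, constrain arm means to be equal at weeks 0 and 12, which keeps patients without a week-12 value. Give the week-0-only model as a sensitivity analysis.
- Do not re-base the change to week 12. A separate week 12 to 96 arm difference is not needed: with arm means constrained equal at week 12, it is the same quantity as the week-96 difference.

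The cost is a change of analysis wording, fixed before outcome data are seen, and one operational line on the order of sampling and disclosure. The sample size need not change. The one downside is that the week-12 covariate is valid only if sampled before disclosure; the week-0-only model covers that risk.

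### 120 per group covers 17.5% missing data, not the stated 20%; at 20% loss, 96 remain per group and power is about 79%, a small shortfall

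*Protocol article*

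**What the plan says.** All the figures stand in the Protocol article under Sample size consideration.

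- Design inputs: the difference is 1%, the SD 2.5% and the test two-sided, with "a type I error rate of 5% and a power of 80" percent.
- Resulting requirement: "it is necessary to include 99 subjects per group in a bilateral situation".
- Loss allowance and planned size: "Because of an estimated data deficiency of 20% at two years (drop out, refusals, deaths), it is planned to include 120 subjects per group". The total is given as 240, and the Abstract also gives two arms of 120.

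The section does not show how 99 became 120.

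Two other places bear on the point. Statistical methods names a two-sided Student t-test by allocated group as the primary analysis, and replaces a missing week-96 HbA1c by the week-84 measurement. Outcomes lists quarterly HbA1c among the secondary outcomes, so late values before week 96 are planned.

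**The concern.** A loss allowance should leave the required number of analysable patients after the expected loss. Here the required number, the loss rate and the planned number are all printed, and any two of them contradict the third. If 20% are lost from 120, the section's own requirement of 99 is missed.

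What is at stake is mainly the accuracy of a stated design figure. A reader who later checks whether observed attrition was within plan would take 20% as the tolerable limit, when the protocol's own numbers put it at 17.5%. The stated power would also be slightly too favourable at the stated loss.

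**Working it through.** **Inputs (Sample size consideration):** difference 1%; SD 2.5%; two-sided type I error 5%; power 80%; 99 required per group; 20% missing at two years; 120 planned per group. Allocation is 1:1 (Randomisation methods). The primary test is a two-sided t-test (Statistical methods).

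**1. Reproduce the plan's 99.** Normal approximation for two means:

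n per group = 2 × (1.960 + 0.842)² × 2.5² / 1² = 98.1, rounded up to 99.

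This matches the printed figure and contains no loss allowance, so 99 is the number needed in the analysis. The discrepancy lies only in the next step.

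**2. Apply the stated loss to the planned size.**

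- Remaining per group: 120 × (1 − 0.20) = 96, which is 99 − 96 = 3 short.
- Loss that 120 can absorb: 1 − 99/120 = 17.5%.
- Size needed to keep 99 after 20% loss: 99 / 0.80 = 123.75, so 124 per group and 248 in total. This is 4 more per group and 8 more overall than planned.
- A possible origin of 120: 99 × 1.2 = 118.8, rounded up.

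**3. Power at the resulting numbers** (difference 1%, SD 2.5%, two-sided 5%).

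Normal approximation: power = Φ(√(n/2) / 2.5 − 1.960). For n = 96 this is Φ(2.771 − 1.960) = Φ(0.811) = 79.1%. The exact figures use the noncentral t distribution with 2n − 2 degrees of freedom.

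| Analysed per group | Loss from 120 | Normal approximation | Exact t |
|---|---|---|---|
| 102 | 15% | 81.5% | 81.1% |
| 99 | 17.5% | 80.4% | 79.97% |
| 96 | 20% | 79.1% | 78.7% |
| 90 | 25% | 76.5% | 76.1% |

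Within either method, going from 99 to 96 costs about 1.2 points of power. Against the nominal 80%, the shortfall is 0.9 points (normal) or 1.3 points (exact t). The difference detectable with 80% power at 96 per group is 1.011% by the normal approximation (2.802 × 2.5 × √(2/96)) and 1.016% by the exact t-test, instead of 1.0%.

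**4. What the week-84 replacement could change.** If the 20% counts missing week-96 values before replacement, 0.20 × 120 = 24 per group are missing. The analysis regains 99 if 3 of those 24 (12.5%) have a week-84 value. If the 20% is what remains missing after replacement, the number stays at 96. The document does not say which applies and gives no figure for the share recovered.

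**The case against.** The strongest defence is the replacement rule. The allowance is described as a shortage of data at two years, HbA1c is to be measured quarterly, and only 3 of 24 missing patients per group would need a week-84 value to restore 99. On that reading 96 is a floor, and the primary analysis could well have its 99. This stands as a possibility but does not repair the text. The allowance is attributed to drop-out, refusals and deaths, and a patient lost before week 84 has no value to carry over. The sample size section neither mentions the rule nor relies on it.

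Two stronger readings are tempting, and the documents support neither.

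- A reader might infer that the trial is underpowered, or that its 80% power is lost. The shortfall is about one percentage point. Part of the gap in the exact figure comes from the choice of method, since the plan's own 99 gives 79.97% by the exact t-test. An SD of about 2.46 instead of 2.5 would cancel it (2.5 / 1.016). A null result would be read mainly from the estimate and its confidence interval, which this hardly alters.
- A reader might take it as established that the allowance was computed as 99 × 1.2. No formula is printed, and 118.8 is not 120. The inconsistency does not depend on how 120 was reached.

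The exact gap to a corrected size also depends on rounding: inflating the unrounded requirement gives 98.1 / 0.80 = 122.6, so 123 per group and a gap of 6 in total instead of 8. On either count 120 is too few for a 20% loss.

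**Conclusion.** The loss allowance is wrong as written, and the error is minor. A requirement of 99, a loss of 20% and a planned 120 per group cannot all hold. This follows from the section's own figures and needs no outside assumption.

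The size of the consequence rests on the plan's inputs (difference 1%, SD 2.5%, two-sided 5%) and on 20% of each group being absent from the primary analysis. On those terms 96 per group gives power of about 79%. If the 20% is counted before the week-84 replacement, the analysed number would exceed 96 by an amount the document does not give, and the shortfall could vanish. Nothing here calls the validity of the trial or its primary analysis into question.

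**What to change.** Keep 240 patients and restate the allowance in Sample size consideration in one of two ways:

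- 120 patients per group allows for 17.5% missing HbA1c values at two years; or
- 120 patients per group with 20% missing leaves 96 per group in the analysis and about 79% power for a 1% difference with an SD of 2.5%.

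In the same place, say whether the percentage is counted before or after week-84 values replace missing week-96 values.

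The cost is one corrected sentence and one added clause. No change to recruitment, conduct or analysis is needed, and the stated allowance or power becomes slightly less favourable. If the sponsor prefers to keep both 20% and 99, the matching size is 124 per group (248 in total), which costs 8 more patients. The small gain in power does not by itself call for that.

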### Randomisation methods

Block randomisation is carried out on two stratification factors: insulin treatment on inclusion (yes/no - two strata), and inclusion centre (five strata). The numbers of participants in each group are balanced with a ratio of 1:1. The 10 randomisation lists are drawn up by the statistician of the CIC-EC of Reunion before the start of the research.

### Blinding

For all patients, the first phase (group-based initial education cycle) will be conducted blind with regard to the randomisation arm for patients, until 12 weeks at the latest, researchers and education team. At the end of this first phase the follow-up will therefore be unblinded.

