## Methods/Design

### Trial design

This is a multicentre open (except during the common initial education cycle) randomised two-arm controlled trial (Figure 1). This trial will be associated with a qualitative ethno-sociological study conducted on a sample of 30–40 persons.

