### Interventions

The patients randomised in both arms will benefit from a structured initial cycle. Trained educators, blind to the subsequent group allocation, will conduct this initial group education cycle within the 12 weeks following inclusion. At the end of these 12 weeks the blinding will be lifted, and the patients randomised in the two-year education arm will continue to receive on-going structured group education. All group sessions will take place at close quarters, organised by the RéuCARE health network in specific locations in each town (municipal and/or community settings).

Patients are reminded by telephone during the week prior to each educational session to confirm the date, time and place. Patients who fail to attend the session will be called within two days and offered a new schedule.

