Self-efficacy, social support and anxio-depressive state will be assessed by means of psychometric scales validated for the purpose of the trial in Reunion. The feeling of self-efficacy will be measured by means of section 3 of the MDQ (Multidimensional Diabetes Questionnaire) [56]. This questionnaire includes 13 items: seven for self-efficacy and six for outcome expectations. The patent’s perception of the specific social support from the partner with regard to the treatment of the diabetes will be assessed on the basis of 12 items derived from the MDQ. The patient’s anxiety will be assessed by the HADS (Hospital Anxiety and Depression Scale) [57]. The HADS includes seven items and is widely used and validated in outpatient prospective studies. The depression level will be measured by means of the CES-D [58,59], which comprises 20 items. The French versions of the two latter tools have demonstrated their psychometric qualities.

The food consumption questionnaire will be conducted face to face with the centre nurse trained for this purpose before the start of the research. The other questionnaires will be self-administered, with the assistance of the study nurse if necessary for subjects with low literacy levels.

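### All follow-up after week 12 is declared unblinded with no outcome assessor exempted, leaving the nurse-conducted food interview (and nurse-assisted questionnaires) open to avoidable interviewer bias

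*Protocol article*

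**What the plan says.** Three sections of the protocol article agree on who knows the arm, and when.

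- Trial design: "This is a multicentre open (except during the common initial education cycle) randomised two-arm controlled trial".
- Interventions: "At the end of these 12 weeks the blinding will be lifted".
- Blinding: the first phase "will be conducted blind with regard to the randomisation arm for patients, until 12 weeks at the latest, researchers and education team", and then "At the end of this first phase the follow-up will therefore be unblinded".

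The Outcomes section describes how the patient-reported secondary outcomes are collected.

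- Timing: "Health practices (level of physical activity and food consumption) will be assessed by means of annual questionnaires". Quality of life is also annual.
- Food: "The food consumption questionnaire will be conducted face to face with the centre nurse trained for this purpose before the start of the research".
- The remaining instruments: "The other questionnaires will be self-administered, with the assistance of the study nurse if necessary for subjects with low literacy levels".

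On the place of education, the Interventions section says: "All group sessions will take place at close quarters, organised by the RéuCARE health network in specific locations in each town (municipal and/or community settings"). Recruitment is in hospital outpatient settings, and patients have quarterly outpatient medical follow-up. The section on concomitant treatments and procedures allows extra individual nursing or dietician contacts in both arms.

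**The concern.** The end of the common cycle explains why patients and educators learn the arm: one group continues with sessions and the other does not. It gives no reason for the person who collects outcomes to learn it. The article nevertheless opens the whole follow-up and makes no exception for assessors. This is a stated design choice, not a detail left out of a condensed article.

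The food interview is the outcome most exposed. The nurse asks about weekly consumption and quantities are judged from a photo album, so there is room to prompt, probe or record differently. Food and control of fat intake are a theme of the programme, and the on-going sessions review the knowledge gained and the actions each patient chose. An interviewer who knows the arm therefore knows which answers the extra sessions encourage. For the self-administered questionnaires the same route exists only in patients who need help. The programme deliberately accommodates such patients with booklets for people with literacy difficulties.

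At stake is whether an arm difference in reported food intake, and to a lesser degree in the assisted scales, can be read as an effect of the intervention.

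**Working it through.** **Step 1: timing.** The blind ends at 12 weeks at the latest. Food and physical activity questionnaires are annual over two years. Apart from the inclusion assessment, every food interview therefore takes place in the open period.

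**Step 2: who must know the arm.** On-going sessions are held at weeks 16, 32, 48, 64, 80 and 96, organised by the network away from the hospital centres. Patients, educators and those who schedule sessions need the allocation. Nothing in the article makes the centre nurse's knowledge necessary for running the sessions. Individual nursing contacts are allowed in both arms, so such a contact does not in itself reveal the arm.

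**Step 3: size, for one continuous measure from the food interview.**

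Inputs:
- 120 patients per arm and 20% missing at two years (Sample size consideration): 120 × 0.80 = 96 evaluable per arm.
- Two-sided 5% test and normal approximation. These are assumed here for a food measure; the article sets 5% two-sided for the primary analysis.
- No true effect, and an interviewer-induced difference d in SD units of the analysed measure. The documents give no value, so d = 0.1 and d = 0.2 are assumptions.

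Smallest difference reaching p = 0.05:
1.96 × √(2/96) = 0.283 SD.

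False-positive rate with shift d, where √(96/2) = √48 = 6.928:
P(Z > 1.96 − 6.928d) + P(Z < −1.96 − 6.928d).

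| d (assumed) | 6.928d | False-positive rate |
|---|---|---|
| 0 | 0 | 5% |
| 0.1 | 0.693 | 0.107, about 11% |
| 0.2 | 1.386 | 0.283, about 28% |

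The value 0.283 appears twice by coincidence: once as a difference in SD and once as a probability.

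**Step 4: why these rates do not carry over to the other questionnaires.** There the nurse can influence only assisted patients. The article gives no proportion assisted. If it were 25% (assumption), a whole-arm shift of 0.1 SD would need 0.1/0.25 = 0.4 SD among those patients, and 0.2 SD would need 0.2/0.25 = 0.8 SD. For a given influence per assisted patient, the whole-arm shift is a quarter as large.

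**Step 5: the plan's own sample size.** A difference of 1%, SD 2.5%, 5% two-sided and 80% power gives 99 per group, as the article states. The point does not depend on this figure.

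**The case against.** The strongest reply is that this is an openly declared open-label behavioural trial with an objective primary outcome, and that it contains no contradiction. That is true, and it limits the consequence to secondary outcomes. It does not explain why the nurse should know the arm.

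Several stronger readings are tempting, and the documents do not support them.

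- *The plan says the nurse is told the allocation.* It does not. The Blinding section names patients, researchers and the education team. The nurse's unblinding is inferred from a general statement that exempts nobody.
- *The nurse collects all questionnaire outcomes.* Only the food questionnaire is an interview.
- *The 12-week blind serves no purpose.* It does serve one. The initial cycle runs from 3 to 7 sessions, chosen partly by each learner, so knowledge of the arm could change effort, session choice or early drop-out. The blind helps keep that phase equal; it does not cover later outcome assessment.
- *Nurse educators will assess their own patients.* The article is silent on this. Separation of staff roles is commonly left to the full protocol, so silence is no finding.
- *Keeping the nurse blind is free and solves the problem.* The article gives no cost or feasibility figure. Patients may disclose their arm, and centre staff may learn it in ordinary care. Patients also report on themselves knowing their arm, and blinding the nurse leaves that bias untouched.

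**Conclusion.** The point holds in a limited form. The article opens all follow-up after week 12 without exempting an outcome assessor, and it places a nurse-conducted interview in that period. Off-site delivery of the sessions means that unblinding patients and educators does not by itself require this nurse to know the arm. The resulting interviewer bias is avoidable in part.

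The food interview is exposed in all patients; the other scales are exposed only in the assisted subset. The rates of about 11% and 28% illustrate the food interview alone and rest on assumed whole-arm shifts of 0.1 and 0.2 SD with 96 evaluable per arm. They do not estimate the bias that will occur, and they should not be quoted for each scale. HbA1c, measured by HPLC in a central laboratory, is not affected.

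**What to change.** Amend the Blinding section so that, after week 12, the existing centre or study nurse who conducts the food interview and assists with questionnaires is not told the allocation until the week-96 assessment is complete. Ask patients not to mention their sessions to this nurse. Have the nurse record at week 96 whether the arm became known. No restriction on the investigating physicians is needed.

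The change is to protocol wording and site instructions and uses existing staff, with no extra visits. The article gives no costing, so low cost is a judgement drawn from the arrangements it describes. The downside is that blinding will be partial because some patients will disclose their arm. The report should say so, and should acknowledge that self-report bias from unblinded patients remains.
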